### Study design and procedure

2.2

This case-control study will be conducted at Wonkwang University Iksan Korean Medicine Hospital in the Republic of Korea. The study has 4 arms: an obese/overweight with AD group, a normal/underweight with AD group, an obese/overweight control group, and a normal/underweight control group. Twenty subjects will be assigned to each arm and a total of 80 subjects will be recruited for this study.

After potential participants voluntarily consent to the study, they will be screened using predetermined inclusion/exclusion criteria at the first visit. To be assigned to a group, subjects will be evaluated based on demographic characteristics, medical history, and physical examination including Hanifin & Rajka AD criteria. The SCORing of AD (SCORAD) index, the Children's Dermatology Life Quality Index (CDLQI), and the Korean Gastrointestinal Symptom Rating Scale (KGSRS); body composition analysis will also be performed to confirm the subjects’ general health and disease status.

The 3-day controlled meal will be provided to the subjects in order to reduce microbial changes due to variable food intake. The 3-day meal is prepared in an allergy-free manufacturing facility and is free of eggs, milk, soy, and wheat, which are known to be the main causes of food allergies.

After the 3-day meal, SCORAD index, CDLQI, KGSRS, and body composition analysis will be evaluated. Blood and fecal samples will be obtained after the controlled meal in order to analyze microbiome-metabolome-immune biomarkers. A fecal sample will also be obtained before the controlled meal in order to assess the microbial differences between the experimental groups before and after the controlled meal. The detailed design is summarized in Figure 1.

**Figure 1 F1:**
[figure not shown]
Flowchart describing the study plan. AD = atopic dermatitis; CDLQI = Children's Dermatology Life Quality Index; KGSRS = Korean Gastrointestinal Symptom Rating Scale; SCORAD = Scoring of Atopic Dermatitis.

### Participants

2.3

Participants defined as having AD are those who satisfy the Hanifin & Rajka AD criteria. Non-AD subjects are those who do not satisfy the Hanifin & Rajka AD criteria and not have asthma, allergic rhinitis, allergic conjunctivitis, or food allergies.

The obese/overweight subjects are those with a body mass index (BMI) at or above the 85th percentile, matched for age and sex. The normal/underweight patients have a BMI at or below the 25th percentile, matched for age and sex. BMI percentile in the same age and sex group is decided based on the World Health Organization (WHO) Child Growth Standards proposed in 2007.

#### Inclusion criteria

2.3.1

1.Boys or girls aged 4 to 12 years old.2.BMI at or above the 85th percentile, or at or below the 25th percentile, matched for age and sex based on the WHO Child Growth Standards proposed in 2007.3.Subjects who can follow the dietary guidelines for 3 days.4.Subjects who agree to participate and voluntarily sign a written informed consent form from the legal representatives and/or participants.

#### Exclusion criteria

2.3.2

1.Severe skin disease or systemic disease.2.Use of oral antibiotics, corticosteroids, anti-histamines, or immunosuppressive drugs within the last 4 weeks.3.Use of prebiotics, probiotics, or herbal medicine within the last 4 weeks.4.Expectation of abnormal defecation during the study period because of constipation.5.Any subject considered unsuitable for participation in the study by the investigator.

#### Recruitment

2.3.3

Subject recruitment began in December 2018 at Wonkwang University Iksan Korean Medicine Hospital and is expected to end by September 2020. The study will be advertised through the hospital, community residences, and local landmarks bulletin boards.

### Variables

2.4

#### Microbiome analysis

2.4.1

Microbiome analysis will be conducted from fecal samples. The deoxyribonucleic acid (DNA) in the collected fecal samples are isolated using the FastDNA SPIN kit (MPBio). PCR will be performed using a primer to amplify the V3–V4 gene region of 16S ribosomal ribonucleic acid (rRNA) from the separated DNA. After purification of the amplified product, a genomic DNA library will be constructed and the nucleotide sequence analyzed.

#### Metabolite profiling

2.4.2

Nuclear magnetic resonance spectroscopy and mass spectrometry will be used to systematically identify and quantify the movement and secretion changes of metabolites in the blood.

#### Immune biomarker analysis

2.4.3

Multiplex immunoassay will be used to analyze the serum Th1/Th2 cytokines including interleukin (IL)-2, IL-4, IL-6, IL-8, tumor necrosis factor (TNF)-α, interferon (IFN)-ɣ, and so on. The total IgE and eosinophil cationic protein (ECP) in the serum will be analyzed. The specific IgE levels for the following 12 specific antigens will be measured using the ImmunoCAP assay: egg white, milk, walnut, wheat, peanut, soy, shrimp, buckwheat, fish (cod), meat mixture, *Dermatophagoides pteronyssinus*, and *Dermatophagoides farinae*.

#### Questionnaires

2.4.4

Questionnaires validated for each purpose and modified to a Korean version will be utilized to measure skin status and its impact on quality of life. The SCORAD index^[13]^ will be used to measure AD severity and the CDLQI^[14]^ will be used to assess the impact of skin disease on the quality of life. The KGSRS^[15]^ will also be examined to assess the severity and frequency of subjects’ gastrointestinal symptoms.

#### Body composition analysis

2.4.5

The body composition test quantitatively analyzes the components of the human body including body water, proteins, minerals, and body fat, to assess the health and obesity status. These factors will be measured by a body composition analyzer (Inbody 3.0; Biospace, Seoul, Republic of Korea).

#### Laboratory analysis

2.4.6

To check subjects’ health status, the following parameters will be analyzed in blood samples: white blood cell (WBC) and differential count (neutrophil, lymphocytes, monocytes, eosinophils, and basophils), red blood cell (RBC), hemoglobin, hematocrit, platelets, mean corpuscular volume (MCV), mean corpuscular hemoglobin (MCH), mean corpuscular hemoglobin concentration (MCHC), erythrocyte sedimentation rate (ESR), hemoglobin A1c, serum glucose-fasting, total cholesterol, high density lipoprotein (HDL)-cholesterol, low density lipoprotein (LDL)-cholesterol, aspartate aminotransferase (AST), alanine aminotransferase (ALT), γ-glutamyl transpeptidase (γ-GTP), total bilirubin, direct bilirubin, indirect bilirubin, alkaline phosphatase (ALP), blood urea nitrogen (BUN), creatinine, triglyceride, total protein, albumin, lactate dehydrogenase (LDH), and creatine kinase (CK).

### Statistical plan

2.5

The participants’ characteristics will be summarized using means and standard deviations for continuous variables that satisfy normality or using median and interquartile range for non-normal data. Group differences will be assessed using 1-way analysis of variance (ANOVA) or the Kruskal–Wallis test. In addition, the independent-samples t-test or chi-squared test will be used to analyze differences between the AD and non-AD groups, as well as between the obese and non-obese groups.

The microbiome sequencing data obtained from feces will be analyzed using the Quantitative Insights into Microbial Ecology (QIIME) and assigned to an operational taxonomic units (OTU) table generated using the EzTaxon database. The Phylogenic Investigation of Communities by Reconstruction of Unobserved States (PICRUSt) program will be used to compare differences in gene expression. Alpha diversity metrics include the number of OTUs (species richness), the Simpson or Shannon diversity indices, and the Chao1 metric. Beta diversity will be analyzed using both unweighted and weighted UniFrac distances.

Metabolome data will be analyzed using univariate statistics and multivariate modeling. All analyses will be implemented in R statistical programming. Statistical differences among groups will be independently evaluated for known and unknown metabolites, and cluster analysis will be used to compare the metabolites profiles. Metabolites displaying significantly altered delta values (*P* <.05) will be used for principal components analysis (unsupervised) and orthogonal partial least squares analysis (supervised) projection to latent structures.

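### Non-normal variables are given a rank test in the four-group comparison, but only a t-test is named for them in the two-group contrasts

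*Protocol article*

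**What the plan says.** All the relevant text is in the first paragraph of section 2.5, Statistical plan, of the Protocol article.

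- **Description.** Means and SDs are used for variables that satisfy normality; otherwise the plan is "using median and interquartile range for non-normal data".
- **Four groups.** "Group differences will be assessed using 1-way analysis of variance (ANOVA) or the Kruskal–Wallis test". The condition for choosing between the two is not spelled out, but after the preceding sentence the natural reading is normality.
- **Two groups.** "the independent-samples t-test or chi-squared test will be used to analyze differences between the AD and non-AD groups". The same sentence extends these tests to the contrast by obesity status. The chi-squared test serves categories, so the t-test is the one method named for continuous variables.

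The rest of section 2.5 covers microbiome and metabolome data. Section 2.4.3, Immune biomarker analysis, lists what is measured: cytokines ("Multiplex immunoassay will be used to analyze the serum Th1/Th2 cytokines"), two further serum markers ("The total IgE and eosinophil cationic protein (ECP) in the serum will be analyzed") and specific IgE to 12 antigens. It names no test, distribution or transformation.

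**The concern.** Three consecutive sentences do not fit together. The first two recognise that some variables will not be normal; the third drops that provision. Followed literally, one variable could be reported by its median, compared across four arms by ranks, and then compared between AD and non-AD children by its mean.

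This is not simply detail left to a fuller document. The article names the two-group test, immediately after naming a parametric and rank pair for four groups.

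What is at stake is efficiency. In a right-skewed variable a few high values inflate the SD and dominate the mean, so a raw-scale t-test may miss a difference that a rank test or a log-scale t-test would detect. Immune concentrations are the obvious candidates. With fixed, small groups, lost power cannot be recovered later.

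**Working it through.** **Inputs**

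- Group size: "Twenty subjects will be assigned to each arm and a total of 80 subjects will be recruited for this study" (section 2.2). 4 × 20 = 80 agrees. Each two-group contrast pools two arms, so it is 20 + 20 = 40 against 40.
- Level: 5% two-sided, an assumption. The article states P < .05 only for selecting metabolites and does not give sidedness.
- Distribution: log-normal with the same log-scale SD, s, in both groups, an assumption. The article gives no SD or distribution, so s is varied.
- The article states no effect size or power, so there is no power figure of its own to reproduce.

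With equal s, the null hypotheses of the raw t-test, the log t-test and Mann–Whitney coincide, so their power can be compared directly.

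**Check 1: effect scaled to the SD.** The log-scale shift is chosen so that a log-scale t-test has 80% power by normal approximation:

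shift = s × (1.960 + 0.842) × √(2/40) = s × 2.802 × 0.2236 = 0.626 s

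The ratio of geometric means is exp(0.626 s). There were 20,000 simulated trials per setting.

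| s | Ratio | Raw t | Mann–Whitney | Log t | Raw t loss v Mann–Whitney | Raw t type I error |
|---|---|---|---|---|---|---|
| 0.5 | 1.37 | 74.0% | 76.4% | 78.6% | 2.4 points | 4.8% |
| 0.75 | 1.60 | 68.3% | 77.3% | 79.6% | 9.0 points | 4.6% |
| 1.0 | 1.87 | 60.0% | 76.6% | 78.9% | 16.6 points | 4.1% |
| 1.25 | 2.19 | 51.4% | 76.9% | 79.3% | 25.5 points | 3.6% |
| 1.5 | 2.56 | 42.3% | 76.4% | 78.7% | 34.1 points | 3.2% |

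Welch's version of the raw t-test does not help: 59.6% at s = 1.0 and 41.4% at s = 1.5.

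**Check 2: fixed two-fold shift**, 6,000 simulated trials per setting. Repeat runs moved individual figures by up to about 2 points.

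| s | Raw t | Mann–Whitney | Log t | Raw t loss v Mann–Whitney |
|---|---|---|---|---|
| 0.8 | 91% | 96% | 97% | 5 points |
| 1.0 | 69% | 85% | 87% | 16 points |
| 1.2 | 47% | 70% | 72% | 23 points |
| 1.5 | 25% | 51% | 53% | 26 points |

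Here every test weakens down the table because the SD grows while the shift stays fixed. Only the gap within a row is due to the choice of test.

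**Cost on normal data.** With the same standardised shift of 0.626 and normal values, the t-test has 78.4% power and Mann–Whitney 76.3%, a cost of 2.1 points.

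**The case against.** **The wording does not say raw scale.** A reader might infer that the plan forbids anything but a t-test on untransformed values. It does not: a t-test on logged values would satisfy the sentence and, in Check 1, keeps about 79% power throughout. This stands. The loss follows from a raw-scale reading, which is the literal one because no transformation is mentioned, but not the only one. Leaving the scale open also leaves it to be chosen after the data are seen.

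**The skewness is not in the documents.** A reader might infer that IgE, ECP and cytokines will lose much of their power. The article gives no distribution for them, and it only makes conditional provision for non-normal data. At s = 0.5 the loss is about 2 points. The size must therefore stay conditional.

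**The paragraph may not govern immune markers.** It opens with participants' characteristics and names no marker. It is applied to them by elimination, since the other two paragraphs deal with the microbiome and the metabolome. That reading is reasonable but not certain. The mismatch between the sentences exists whichever variables they cover.

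**The contrasts are not designated as main.** The article introduces them as an addition to the four-group comparison and names no primary contrast. They are better described as direct comparisons on the two factors that define the arms.

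**Conflicting results prove little.** An omnibus four-group test and a pooled two-group test address different hypotheses and can disagree even when both use ranks. Disagreement between them is not itself evidence of a fault.

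**Transformations usually belong in an analysis plan.** True of a full list of transformed variables. It does not excuse a stated test that does not match its neighbouring sentences.

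**Conclusion.** The inconsistency holds: non-normal variables have a rank test across four groups and none named in the two-group contrasts. Its consequence is possible inefficiency, not invalidity. In these simulations the raw t-test becomes conservative under skew, so nothing supports a claim of excess false positives.

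The size rests on log-normal markers with equal log-scale SDs, 40 against 40 and a two-sided 5% level. Across both checks the loss against Mann–Whitney is small for mild skew (about 2 to 9 points at s = 0.5 to 0.75) and substantial for strong skew (about 15 to 35 points at s = 1.0 to 1.5). The documents do not show where in this range any marker lies. The change is still worth making, because it costs little and settles the choice of test in advance.

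**What to change.** Replace the two-group sentence for continuous variables with wording such as:

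> Two-group contrasts of continuous variables use the independent-samples t-test where ANOVA is used and the Mann–Whitney U test where Kruskal–Wallis is used. Total and specific IgE, ECP and cytokines are log-transformed before ANOVA and the t-test, in both the four-group and the two-group comparisons, with effects reported as ratios of geometric means.

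Keep the chi-squared test for categorical variables. Naming the log-scale markers now means that the choice between a log-scale t-test and Mann–Whitney is not left open for them. The log scale also needs a stated rule for any value reported as zero or below an assay limit.

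No extra subjects, samples or visits are needed. The costs are about 2 points of power if Mann–Whitney is applied to truly normal data, and effects expressed as ratios or rank shifts instead of differences in raw means.

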**Methods and analysis::**

A case–control study will be conducted in the Republic of Korea. A total of 80 subjects, aged 4 to 12 years, matched for age and sex, with body mass index at or above the 85th percentile or at or below the 25th percentile, will be included. Subjects will be assigned to the following 4 groups: obese/overweight with AD, normal/underweight with AD, obese/overweight control, and normal/underweight control. Serum metabolome and immune biomarkers, as well as fecal metabolome and microbiome biomarkers, will be analyzed. Serum eosinophil cationic protein, total serum Immunoglobulin E (IgE), and specific IgE will be analyzed to assess allergic tendency. The SCORing of AD index, the children's dermatology life quality index, body composition analysis, and the Korean gastrointestinal symptom rating scale will be obtained to assess the disease status and severity of the subjects.

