## Discussion

3

This is a study protocol to investigate the association of AD with obesity in the Korean population and verify its mechanism by analyzing gut microbiome–metabolome–immune biomarkers using a multi-omics approach.

In this study, we included 4 to 12-year-old children as subjects for several reasons. First, AD is one of the most common chronic childhood skin diseases, affecting up to 15% to 20% of children worldwide.^[16,17]^ Given that the symptoms of AD usually begin in infancy, the majority of AD cases develop before the age of 5 years,^[18,19]^ and the prevalence in teenagers seems to be falling significantly,^[20]^ children aged 4 to 12 have a high prevalence of AD. Second, most children aged 4 to 12 years in Korea, spend most of their time in a group setting, such as a kindergarten or school, eating a similar Korean-style diet consisting of rice, soup, and side dishes. Third, it is known that the phylogenetic composition of bacterial communities evolves towards an adult-like composition within 3 years after birth.^[21]^

In the present study, a 3-day controlled diet will be provided to ensure better dietary control, and fecal samples will be collected both before and after controlled meals. It is now understood that diet plays a significant role in shaping the microbiome, with experiments showing that dietary alterations can induce large, temporary microbial shifts within 24 hours.^[22,23]^ Because there is no appropriate guideline in terms of dietary control in microbiome analysis, we assumed that 3-day-controlled meal is sufficient to eliminate effects of diet. We also will analyze microbial changes before and after the 3-day meal to confirm whether the 3-day controlled meal is sufficient to remove microbial changes due to diet.

This study protocol represents a unique opportunity to enhance our understanding of the association between AD and obesity in terms of gut microbiome, metabolome, and immunological mechanisms and may, therefore, serve to improve future management strategies for AD.

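### Entry to PCA and OPLS depends on an undefined delta that, read as pre-to-post change, cannot be computed for serum because blood is taken only after the meal

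*Protocol article*

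**What the plan says.** The last sentence of the Statistical plan (2.5) sets the entry rule for the two multivariate metabolome models, PCA and OPLS. The metabolites that go in are "Metabolites displaying significantly altered delta values", judged at P < .05. The section does not say what delta is: no matrix, time points or contrast is given. An earlier sentence in the same paragraph plans separate group tests: "Statistical differences among groups will be independently evaluated for known and unknown metabolites". Cluster analysis is also planned.

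The sampling is in Study design and procedure (2.2): "Blood and fecal samples will be obtained after the controlled meal in order to analyze microbiome-metabolome-immune biomarkers". One specimen is added before the meal, with its own purpose: "A fecal sample will also be obtained before the controlled meal in order to assess the microbial differences between the experimental groups". The Discussion gives the reason for the before-and-after comparison: "We also will analyze microbial changes before and after the 3-day meal to confirm whether the 3-day controlled meal is sufficient" to remove the microbial effect of diet.

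Metabolite profiling (2.4.2) names one matrix. The assays are to "quantify the movement and secretion changes of metabolites in the blood". The abstract goes further: "Serum metabolome and immune biomarkers, as well as fecal metabolome and microbiome biomarkers, will be analyzed".

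**The concern.** The rule and the sampling scheme do not fit together. In a study with a before-and-after meal step, delta would ordinarily mean change across that step. The only matrix that 2.4.2 assays for metabolites is blood, which is collected once. Someone applying the rule would have to decide what delta stands for, probably with the data in hand, and that decision fixes which metabolites the PCA and OPLS results are built on.

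Feces is the one matrix with two time points, so a fecal delta is the obvious substitute. It answers a different question. The Objectives (2.1) concern the association of AD with obesity and its mechanism. A metabolite that is consistently higher in children with AD, before and after the meal, has no expected change and would usually be filtered out.

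**Working it through.** The plan states no figure on this point to reproduce. The check has three steps.

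**1. Samples per child, from 2.2**

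| Matrix | Before meal | After meal | Pre-to-post change possible? | Metabolites assayed? |
|---|---|---|---|---|
| Blood | 0 | 1 | No | Yes (2.4.2) |
| Feces | 1 (for microbial differences) | 1 | Yes | Abstract only; not in 2.4.2 |

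The matrix with a described metabolite assay has no change score. The matrix with two samples has no described metabolite assay, and its first sample is given another purpose.

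**2. What a change score would select**

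Let D be a stable AD difference, T a meal effect common to all children, and I an extra meal effect in AD, all in SD units. Relative to non-AD at baseline:

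- AD: pre = D, post = D + T + I, so mean delta = T + I.
- Non-AD: pre = 0, post = T, so mean delta = T.

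D cancels within the AD group. The between-group difference in delta is I alone. The post-meal difference is D + I. If T = I = 0, any test on delta rejects at about its alpha of 5%, however large D is.

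Illustration: four arms of 20 give 40 AD and 40 non-AD; two-sided 0.05; 3,000 simulated data sets per scenario. The effect sizes and the pre/post correlations (0.3, 0.6, 0.8) are assumptions, not from the protocol. Cells show the chance of selection at P < .05 across the three correlations.

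| Scenario | Post-meal level, between groups | Delta, within subjects against zero | Delta, between groups |
|---|---|---|---|
| Stable AD difference, D = 0.8 | 94% | 5–6% | 5% |
| Common meal effect, T = 0.5 | 5% | 96–100% | 5–6% |
| Meal effect differing by AD, I = 0.8 | 94% | 83–100% | 85–100% |

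Check on the first cell by the normal approximation: 0.8 × √(40/2) = 3.58; 3.58 − 1.96 = 1.62; power about 95%.

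**3. Why a between-group P-value filter is not a safe replacement**

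If delta is read as a between-group difference, post-meal serum can supply it, but the same labels then choose the metabolites and are displayed or predicted by the model. This was simulated with pure-noise metabolites, 40 against 40, 500 runs, a P < .05 filter applied to the full data, then a one-component PLS-type classifier (standing in for OPLS) with 7-fold cross-validation. The number of metabolites is an assumption.

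| Noise metabolites | Expected to pass (5%) | Cross-validated accuracy after filter | Without filter |
|---|---|---|---|
| 100 | 5 | about 69% | 48–50% |
| 300 | 15 | about 80% | 48–50% |
| 1,000 | 50 | about 94% | 48–50% |

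After the filter, the first principal component separated the groups at P < .05 in 88–100% of runs, although there was nothing to find.

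**The case against.** The strongest reply is that delta is not defined as a change over time. The group-difference sentence comes just before it, so delta could mean a difference between groups, which a single post-meal blood sample can supply. That reading is possible, and it rules out saying flatly that no serum delta exists for any of the 80 children. It does not rescue the rule. With four groups the difference needs a named contrast and none is given, and step 3 shows that a group filter ahead of PCA and OPLS is circular.

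A reader might also infer that the rule would pick diet-responsive metabolites instead of AD- or obesity-related ones. The protocol does not support that. It holds only if deltas are tested within subjects against zero, and no such test is stated. Compared between groups, a common meal effect is selected only about 5% of the time, and what is selected is a meal response that differs by group. The loss of stable differences holds under both tests. Even so, a fecal metabolite delta is only a possibility, because the pre-meal sample is not assigned to metabolomics.

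Two further replies have weight. The wording in 2.4.2 about changes may be a loose description of metabolomics and not a claim of paired samples. And a condensed article may leave assay detail to the full protocol, so the missing fecal assay is a mismatch to reconcile, not proof that none is planned. The entry rule itself is different: the article states it.

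**Conclusion.** The point stands in limited form. Delta is undefined. On its ordinary reading it cannot be computed for serum under the sampling in 2.2. If a fecal delta were substituted, stable AD or BMI-group differences would pass the filter at about the false-positive rate (5–6%, against about 94% for a post-meal comparison at an assumed 0.8 SD).

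The defect is confined to what enters PCA and OPLS. A reader might conclude that the whole metabolome analysis has no input; it does, because the univariate group tests and the cluster analysis run on post-meal levels without any delta.

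The sampling count rests on the text of 2.2; Figure 1 is not shown and could not be checked. The percentages rest on assumed effects, correlations and metabolite counts and show direction and rough size only. The cancellation of a stable difference does not depend on them. Because the rule decides which variables the multivariate models see, it should be settled before the metabolome data are analysed.

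**What to change.** - **2.5, selection rule:** replace the delta rule with post-meal metabolite levels and name the contrasts: AD, BMI group, and AD × BMI group.
- **2.5, PCA and OPLS:** run PCA on all measured metabolites that pass quality control. Do not pre-filter by a group P value before OPLS; if selection is wanted, do it inside the cross-validation or permutation loop.
- **Fecal change:** use any pre-to-post fecal change only for the diet check described in the Discussion.
- **2.4.2:** align the word changes with the single post-meal blood sample.
- **2.4.2 and abstract:** reconcile them, either by describing the fecal metabolite assay or by removing the fecal metabolome from the abstract.

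Cost: wording in 2.4.2 and 2.5 (and possibly the abstract), and no extra blood draw. The multivariate models will be less sparse, and the analysis takes slightly more work. Fecal assays are an added cost only if the abstract's promise is kept and they are not already planned.

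### PCA and OPLS are confined to metabolites that already passed P<.05; if that test compares the groups, as the text most plausibly means, the separation they show is circular

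*Protocol article*

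**What the plan says.** All of this is in the Protocol article.

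- Section 2.5 first sets the metabolite-by-metabolite tests: "Statistical differences among groups will be independently evaluated for known and unknown metabolites".
- It then sets the entry rule for the multivariate models: "Metabolites displaying significantly altered delta values (*P* <.05) will be used for principal components analysis (unsupervised) and orthogonal partial least squares analysis (supervised"). The article therefore fixes the selection step, its threshold and the two models that receive the survivors. This is not a detail left open for an analysis plan.
- The group tests named earlier in section 2.5 are a four-group test, "Group differences will be assessed using 1-way analysis of variance (ANOVA) or the Kruskal–Wallis test", and two-group comparisons, "the independent-samples t-test or chi-squared test will be used to analyze differences between the AD and non-AD groups", with a matching comparison by obesity.
- Section 2.2 gives the numbers, "Twenty subjects will be assigned to each arm and a total of 80 subjects will be recruited for this study", and the sampling: "Blood and fecal samples will be obtained after the controlled meal" and "A fecal sample will also be obtained before the controlled meal in order to assess the microbial differences". No pre-meal blood sample is described.
- Section 2.4.2 describes the metabolite platform for blood: "Nuclear magnetic resonance spectroscopy and mass spectrometry will be used to systematically identify and quantify the movement and secretion changes of metabolites in the blood". The Abstract also lists a fecal metabolome.

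The article does not define delta, does not say whether the P<.05 is adjusted, and does not give the number of metabolites.

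**The concern.** A PCA is unsupervised only if group membership plays no part in building it. If metabolites are admitted because they differ between the groups in these children, every admitted variable already carries a group difference. The leading components will then tend to show that difference, whether it is real or chance. The reader of the score plot is told that the method did not use the labels, when the labels chose its inputs.

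OPLS uses the labels openly, so its in-sample fit is optimistic in any case. The particular harm of the screen is that it also spoils the usual safeguard. Cross-validation run after the filter holds out children who have already helped to choose the variables.

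The study aims to verify a mechanism through microbiome, metabolome and immune markers (section 2.1). Separation on a PCA or OPLS plot that arises readily from null data would be weak support for that aim.

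**Working it through.** **Which test the screen uses.** Three readings of delta are possible.

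1. *A difference between groups.* This fits the preceding sentence in section 2.5, and it fits serum, for which only one sample is described. The selection is circular.
2. *A before-after change in feces, compared between groups.* Fecal samples exist at both times. The selection still uses group labels and is equally circular.
3. *A before-after change tested against zero, ignoring group.* The selection is not circular. It cannot apply to serum sampled once, and the stated purpose of the pre-meal fecal sample is microbial.

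**Inputs.** From the article: 4 groups × 20 = 80 children, so 40 v 40 for AD against non-AD; threshold P<.05. Assumed: two-sided tests; M = 50 to 500 metabolites, either independent or correlated 0.5 in blocks of 10. The article has no figure of its own to reproduce here.

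**Why separation follows.** With 40 v 40, the t-test has 78 degrees of freedom and a critical value of about 1.99. A metabolite passes only if its observed group difference is at least 1.99 × √(1/40 + 1/40) = 1.99 × 0.224 ≈ 0.45 SD. So every variable in the PCA has a sample difference of at least that size, even when the true difference is zero.

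**How many null metabolites pass.** The expected number is 0.05 × M. For independent metabolites, P(at least two) = 1 − 0.95^M − M × 0.05 × 0.95^(M−1):
- M = 50: 1 − 0.077 − 0.202 = 0.72
- M = 100: 1 − 0.006 − 0.031 = 0.96
- M = 200: above 0.999

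**Null simulation**, 200 datasets per setting. Metabolites were screened by t-test (AD against non-AD) or by four-group ANOVA. PCA was run on the survivors, and PC1 and PC2 were tested for a group difference with a Bonferroni factor of 2. Ranges cover both correlation settings; the second column also covers both screens.

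| M | Expected to pass | Two or more pass | PC1/PC2 separate, t-test screen* | PC1/PC2 separate, ANOVA screen* | No screen | Group-blind change screen* |
|---|---|---|---|---|---|---|
| 50 | 2.5 | 59-73% | 96-98% | 97-98% | 4-6% | 5% |
| 100 | 5 | 88-97% | 98-99% | 97-98% | 4-7% | 4-7% |
| 200 | 10 | 99-100% | 100% | 98-99% | 1-6% | 2-7% |
| 500 | 25 | 100% | 99-100% | 100% | 4-5% | 3% |

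*Among datasets with two or more survivors.

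Over all null datasets, the proportion with separation is the product of the two columns. At M = 50 it runs from 0.59 × 0.98 = 58% to 0.73 × 0.96 = 70%. At M = 100 it runs from 0.88 × 0.98 = 86% to 0.97 × 0.97 = 94%. The separation also strengthens with M. After the t-test screen it reaches P<.001 in 17-52% of analysable datasets at M = 50 and in 99-100% at M = 500.

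**Supervised model.** A two-component PLS discriminant fit (equivalent in fit to OPLS with one predictive and one orthogonal component) was cross-validated in 7 folds after the filter, with AD against non-AD as the outcome.
- t-test screen: mean Q2 0.06-0.10 at M = 50, 0.09-0.17 at 100, 0.17-0.26 at 200 and 0.35-0.47 at 500; above zero in 86-100% of analysable datasets.
- ANOVA screen: weaker, from about zero at M = 50 to 0.18-0.24 at M = 500.
- No screen: mean Q2 between −0.17 and −0.57. The in-sample R2 was nevertheless 0.39-0.98, so fit alone is uninformative even without the filter.
- A separate run at M = 300 with one component: Q2 0.28-0.41 with the filter outside the folds, and −0.33 with it repeated inside each fold.

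**False discovery rate screening.** With Benjamini-Hochberg at 5%, two or more metabolites survived in only 0-3% of null datasets, but PC1 or PC2 separated the groups in all of those. It makes the artefact rare without removing the circularity.

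**The case against.** The strongest objection is that the argument turns on a word the article does not define. Fecal samples are taken before and after the meal, and a fecal metabolome is planned. A group-blind change score is therefore possible for feces, and under it PC separation falls to 2-7%. This stands as a reason to state the point conditionally and to require a definition. It does not rescue serum, and it sits poorly with the sentence just before the rule.

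A reader might also infer more than the text supports:

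- *That separation will appear whatever the truth.* The number of metabolites is not given. At 50, roughly 30-40% of null datasets would show no separation, mostly because fewer than two metabolites pass. Separation becomes near-certain only at about 100 metabolites or more.
- *That the P<.05 is certainly unadjusted.* The threshold is bare and no correction is named, but a condensed article may leave that to the analysis plan. The circularity does not depend on it.
- *That reported validation will be inflated.* The article describes no cross-validation, so the Q2 figures show what would happen if it were run after the filter.
- *That the metabolomic result as a whole is void.* Univariate tests and a cluster analysis are also planned, and no primary outcome or decision is tied to the score plots.
- *That FDR control is missing for taxa, pathways, cytokines and specific IgE.* Section 2.5 sets no significance threshold for these, and the matter belongs to the analysis plan.

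**Conclusion.** The point holds in conditional form. On the between-group reading, which is the likeliest one, the rule selects variables with the labels of the same 80 children and then displays those children on the selected variables. The PCA is not unsupervised. The OPLS fit is optimistic, and so is any cross-validation run after the filter.

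Under no true difference, PC1 or PC2 separates the groups in about 96-100% of datasets with two or more survivors, against about 1-7% without the screen.

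This rests on an assumed 50 to 500 metabolites, two-sided tests, simulated data with independent or block-correlated metabolites, and a single blood sample as section 2.2 describes (Figure 1 was not available for this check). The conclusion covers separation in PCA and OPLS only. It does not reach the univariate tests or the cluster analysis.

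**What to change.** Change the last sentence of section 2.5, and carry the change into the analysis plan, before the metabolome data are analysed:

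1. Define delta for serum and for feces: which two quantities are subtracted, and whether group enters the test.
2. Run PCA on all metabolites that pass quality control, with no selection on group P values.
3. Run OPLS on all of them as well, or, if selection is wanted, repeat it inside every cross-validation fold. Give a permutation P for the whole pipeline, selection included (for example 1,000 label permutations), and do not rely on in-sample fit.
4. If the P<.05 is unadjusted, use a Benjamini-Hochberg false discovery rate for the univariate metabolite list. State that this serves the list only and does not make it safe to feed the survivors to PCA or OPLS.

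The cost is a few lines of R, with no new children, samples or assays. The downside is fewer flagged metabolites and less striking score plots.
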